## Abstract

**Introduction:**

Obesity in women has more than doubled in the past thirty years. Increasing research suggests that increased cardiorespiratory fitness (CRF) can largely attenuate the negative health risks associated with obesity. Though previous literature suggests that combined training may be the most effective for improving CRF in adults with obesity, there is minimal research investigating the efficacy of combined and resistance programmes in women with obesity. This article outlines a protocol for a parallel pilot study which aims to evaluate the feasibility and efficacy of three exercise modalities in women with obesity for increasing CRF and strength and improving body composition and other health outcomes (i.e. quality of life).

**Methods and analysis:**

Sixty women (aged 18–50) with obesity (body mass index [BMI] ≥ 30 and/or waist circumference ≥ 88 cm) who are physically inactive, have no unstable health conditions and are safe to exercise will be recruited from September 2021 to December 2022. The main outcome will be feasibility and acceptability of the intervention and procedures. Trial feasibility outcomes will be evaluated to determine if a definitive trial should be undertaken. Trial acceptability will be explored through follow-up qualitative interviews with participants. Secondary outcomes will include CRF (predicted VO_2_ max), anthropometrics (i.e. BMI), strength (5RM bench press, leg dynamometry, grip strength) and other health outcomes (i.e., pain). Participants will be block randomised into one of four trial arms (aerobic exercise, resistance training and combined training groups, non-active control group) and measurements will be completed pre- and post-intervention. The exercise groups will receive an individualised supervised exercise programme for 3× sessions/week for 12 weeks. The change in mean values before and after intervention will be calculated for primary and secondary outcomes. ANOVA and *t*-tests will be applied to evaluate within-group and between-group differences. If sufficient participants are recruited, the data will be analysed using ANCOVA with the age and BMI as covariates.

**Discussion:**

This pilot will provide data on the feasibility and acceptability of trial procedures and of the programmes’ three progressive time-matched exercise interventions (aerobic, resistance and combined) for women living with obesity, which will help inform future research and the potential development of a full-scale randomised clinical trial.

**Trial registration:**

ISRCTN, ISRCTN13517067. Registered 16 November 2021—retrospectively registered.

## Background

Despite decades of awareness of the obesity challenge, this chronic disease continues to prevail as one of the world’s leading causes of morbidity and mortality [1, 2]. Women, in particular, appear more susceptible to obesity, with the prevalence of female obesity having more than doubled in the past 30 years and the prevalence of morbid obesity in women more than twice that recorded in men [3]. Evidence suggests that among adults, young women of childbearing age (18–44 years) are the most at risk of developing obesity [4, 5], with this cohort demonstrating the highest rate of weight gain [6–10]. Furthermore, the adverse effects associated with obesity appear to be greater in women, with the risks of developing cancer and cardiovascular and metabolic disorders significantly higher than observed in men [11–15]. Mounting evidence highlights the strong association between excessive weight gained during early childbearing years and longer-term adverse health outcomes [4, 16–18].

Encouragingly, increasing literature indicates that improvements in cardiorespiratory fitness (CRF), attainable through exercise, can largely attenuate the health-related risk factors, regardless of obesity severity [19–23]. Noteworthy, however, is that women, particularly young women, are significantly less active than their male counterparts [19, 20, 24, 25]. Globally an estimated 1 in 3 women do not meet generic exercise guidelines (150 min/week of moderate-intensity aerobic exercise, × 2 days/week of moderate-high intensity resistance training), with some country-specific statistics indicating that closer to 1 in 2 women aged 18–54 not meeting these recommendations [26–30]. This physical inactivity has been shown to strongly correlate with excessive weight gain in the short term and the development of cardiovascular risk factors over the longer term in this cohort [5, 31–33]. Alongside physiological differences between men and women (i.e. body size, muscle and fat mass, cardiac output etc.) [33–36], physical inactivity as a behaviour, has been identified as a stronger determinant of CRF in women [37], with the literature reporting an estimated average difference in CRF up to 20% between the sexes (in both active and inactive adults) [37–39].

To date, it is unclear how this difference in CRF translates to sex-specific responses to exercise training in the context of obesity. Evidence based on normal weight, healthy adults, suggests that males demonstrate greater increases in both absolute and relative maximal oxygen uptake (VO_2_ max) in response to training, and highlights a more blunted adaption to training in females [40, 41]. Most literature investigating the efficacy of exercise in women with obesity has primarily focused upon the prescription of interventions based upon generic physical activity guidelines, where moderate-intensity aerobic exercise is advocated. Although most of the studies focus on weight loss, the few that include CRF as an outcome measure, have observed small to moderate improvements in CRF [42–45]. Previous literature, including a recent network meta-analysis, indicate that combined (aerobic and resistance) interventions (particularly high intensity) are the most promising for improving CRF and body composition in adults living with obesity [46, 47]. However, most of the available studies which investigated resistance training or combined training were in men. Additionally, a recent systematic review and meta-analysis (conducted by this protocol’s author [[name]] and colleagues) which focused solely on women with obesity, further highlighted both the paucity of well-designed exercise intervention studies focused on young women with obesity and the lack of research investigating CRF and other measures of health such as quality of life, pain and mood.

### Aims and objectives

Therefore, the primary aim is to evaluate the feasibility and acceptability of prescribed time-matched aerobic, resistance and combined interventions (targeting changes in cardiorespiratory fitness) in women with obesity and to inform whether a future definitive trial could or should be undertaken. We will assess recruitment challenges; retention rates, attendance rates and adherence of participants to prescribed programme, incidence of adverse events and participant’s experience of the intervention and the acceptability of trial procedures and the programmes. We will also collect data from which a power calculation can be based to determine the number of participants needed per group in order to achieve significance in a potential follow-up randomised controlled trial (RCT).

The secondary objectives are to determine the mean difference between groups (three exercise groups and a non-exercise control group) at 12 weeks in:(i)CRF (predicted VO_2_ max)(ii)anthropometric outcomes (Body mass index (BMI), percentage body fat (%BF), lean mass (LM), fat mass (FM), waist-hip ratio (WHR) and waist circumference (WC)(iii)strength (five repetition maximum [5RM] bench press, leg dynamometry, grip strength)(iv)self-reported quality of life, physical activity, sedentary time, sleep, mood and pain

### Hypotheses tested

Primary null hypothesis: Post intervention, there is no difference in outcomes (CRF, strength, body composition, self-reported) between participants randomised to the exercise interventions and the control.

Secondary null hypothesis: Post intervention, there is no difference in outcomes (CRF, strength, body composition) between participants randomised to the aerobic exercise, resistance training and combined training groups.

## Methods

### Quantitative study

#### Trial design

This four-arm parallel pilot study has been approved by University College Dublin (UCD) Human Research Ethics Committee (LS-21-59-[name]) and will be reported in line with the Consolidated Standards of Reporting Trials (CONSORT) guidelines extension for randomised pilot and feasibility trials [48] and the Standard Protocol Items: Recommendations for Interventional Trials (SPIRIT) [49]. Following initial screening, the participants will be randomised with an allocation ratio of 1:1:1:1 into one of the three time-matched exercise modes or control (Figs. 1 and 2).Aerobic: progress to 150 min/week of continuous aerobic exercise at 75–80% HRRResistance training: progress to 150 min/week of 3–6 × 12 reps of resistance exercise at 75–80% 1-RMCombined training: progress to a 50:50 split of combined aerobic (75–80% HRR) and resistance (3–6 × 12 reps, 3 exercises at 75–80% 1RM) training for 150 min/weekControl: non-exercise group (participants to maintain baseline physical activity levels)

**Fig. 1 Fig1:**
[figure not shown]
Participant flow through the pilot (based on CONSORT statement)

**Fig. 2 Fig2:**
[figure not shown]
Schedule of enrolment, interventions, and assessments (based on SPIRIT protocol)

#### Study setting

The study will be conducted in University College Dublin (UCD) in Dublin, Ireland from September 2021 to December 2022. Baseline/follow-up assessments and all exercise intervention arms will take place in UCD Institute for Sport and Health (ISH).

#### Participants

Participants will be recruited using a flyer which will be distributed in UCD internal networks, on social media platforms and in local areas (clinics, health centres, pharmacies) and shared with the chairperson of the Irish Coalition for People Living with Obesity (ICPO) with its members. Interested participants will be encouraged to contact the trial coordinator ([name]) who will complete eligibility screening over the telephone using the criteria detailed in Table 1 to evaluate a participant’s eligibility and individual safety for starting an exercise programme using the Physical Activity Readiness Questionnaire for Everyone (PAR-Q+). If screened as eligible, potential participants will receive the study information sheet and consent form by email or by post (preferred method). All consenting participants will be invited to ISH for baseline assessment a minimum of seven days later (cooling off period) (Fig. 2).

**Table 1 Tab1:** Eligibility criteria for inclusion in trial

Criterion	Characteristics of eligible participants
1	Female aged 18-50 years at time of consent
2	Have a Body Mass Index (BMI) ≥ 30 kg m^−2^ and /or a waist circumference > 88 cm
3	Are currently physically inactive (exercising less than 150 min/week)
4	Have not undergone weight loss surgery or another surgery in the past 3 months
5	Not pregnant (or within 6 months post-pregnancy) or lactating
6	Do not have a significant mental illness or cognitive deficits
7	Are not participating in another trial (exercise-based or targeting weight-loss) at time of consent
8	Are not contraindicated or no clinician (i.e. GP) has advised them against exercising (i.e. chest pain during activity or at rest, severe hypertension etc.)
9	Do not have an unstable cardiovascular, respiratory, renal or hepatic condition

#### Baseline assessment

On arrival at UCD ISH, the trial coordinator will meet potential participants and provide an overview of the study, an introduction to the tests that will be performed, the equipment that will be used and the purpose of each test. Participants will have the opportunity to ask any questions about the study at this time. Signed consent forms will be collected from willing participants. No study procedures will commence until written consent is obtained.

Sociodemographic and related health information of participants will be collected, including education employment status, medical and exercise participation history. Participants resting blood pressure and heart rate will be measured three times and an average calculated. Blood pressure will be measured on the upper arm using a wireless blood pressure monitor (make: Omron; model: Evolv) prior to the test. For participants where the bicep cuff is undersized, a wrist monitor will be used (make: Omron; model: R57 Intelli IT). In order to be eligible to continue to exercise testing, participants must have a resting blood pressure ≤ 160/100 (grade 2 hypertension) [50]. Once there are no contraindications to exercise testing recorded [51], objective measures of anthropometry, strength and CRF will follow.

##### Anthropometry

The following anthropometric/body composition variables will be collected (body mass index [BMI], body weight [BW], body fat percentage [%BF], waist circumference [WC], lean mass [LM], fat-free mass [FFM], waist-hip ratio [WHR], height). All outcomes will be measured using standard procedure with participants dressed in light, close-fitted clothes and with bare feet. Height, WC and BW will be measured to the nearest 0.1cm and 0.1kg respectively using a calibrated scales, stadiometer and tape measure respectively. Waist circumference will be recorded midway between the top of the pelvic bone and the bottom margin of the last rib using a tape measure [52]. Whole body composition will be measured using a bioelectrical impedance body composition analyser (seca mBCA 515).

##### Muscular strength

In order to measure strength, a 5RM bench press, leg dynamometry and grip strength will be used. To measure repetition maximum for bench press, participants will be instructed on proper form for this exercise and guided through progressive lifts where the weight will be increased in increments of 1.25–2.5 kg as needed until the participant reaches a weight at which they cannot perform all 5 reps of the movement maintaining good form. Fifty seconds of rest will be provided between attempts.

Leg strength will be measured using a back-leg strength dynamometer (Takei Back-D TKK 5402, Takei Scientific Instruments, Japan). Participants will be instructed to stand on the base of the machine, with feet shoulder width apart and their back bent slightly forward at the hips. The length of the chain will be adjusted so that the base of the bar rests superior to the anterior pole of the patella. Looking forward with a straight back, participants will be instructed to pull on the chain as hard as they can for 3 s in one fluid movement. Participants will be instructed to perform this test three times, with a rest of 50 s after each attempt. The maximum weight (kg) of all three attempts will be recorded. Grip strength will be measured using a hand-held dynamometer (Jamar Hydraulic Hand Dynamometer, Performance Health Supply, USA). To perform this measure, participants will be placed in sitting and the dominant arm supported on a side table and positioned with shoulder adducted, neutrally rotated, elbow flexed at 90°, forearm in neutral position and wrist between 0–30° dorsiflexion and 0–15° ulnar deviation [53]. The dynamometer handle will be set to the second handle position from the inside. Participants will be instructed to squeeze the handle for 3 s and will perform the test three times, with a rest of 50 s between attempts. The maximum weight (kg) of all three attempts will be recorded.

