##### Resistance

This intervention consists of 3 × 50-min sessions per week of progressive resistance exercises. During weeks 1–6, session length will gradually progress until participants can perform 3 × 50-min sessions in week 7 (Table 3). The resistance programme contains eighteen exercises, with an equal amount of upper limb (shoulder press, bench press, bicep curl, raise, triceps exercises, bent-over row) core (seated and standing twists, hip bridge, 4-point kneel, overhead ball slam, push-ups) and lower limb (barbell squat, goblet squat, deadlift, Romanian deadlift, lunge, lateral lunge) exercises included. In each session, participants will perform six exercises aimed at targeting all major muscle groups (Table 4). The participants will perform three different exercise regimes on a weekly basis, alternating every second week (Table 5). They will be monitored to track weights lifted and be provided with feedback on correct technique as needed. In weeks 1–2, participants will perform 2 × 12 reps of the six exercises at 40–50% 1RM to allow them to become familiar with the different exercises. From weeks 3 to 4, participants will perform 3 × 12 reps of each exercise at 50–55% 1RM. From weeks 5 to 12, participants will perform up to six sets of each exercise to meet the prescribed time for each session (i.e. 50 min). The load will progressively increase for all exercises performed from weeks 1–12 from 40% 1RM in week one to 80% 1RM in week twelve (Table 3) once a participant can perform all sets of 12 reps with proper form in one session and/or once the participant reports finding the exercise easy. Each set of exercises will be followed by a 45-s rest.

**Table 4 Tab4:** Resistance exercises included in the resistance and combined programmes

Exercise	Variations

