#### Follow-up assessment

During the last week of the 12-week intervention period, all participants will be approached by the trial coordinator to arrange an appointment for a follow-up assessment within seven days post-intervention. Similar to the baseline assessment, participants will be instructed to attend ISH on a separate day after the intervention has ended to have their follow-up assessment following the procedures detailed above. The participants will also be issued the combined set of valid and reliable self-reported outcome questionnaires used pre-intervention.

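### The 5RM bench press climbs in 1.25–2.5 kg steps with 50 s of rest and no stated limit on attempts, so the recorded load can reflect accumulated fatigue as well as strength

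*Protocol article*

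**What the plan says.** The Muscular strength section of the protocol article describes an ascending test. After instruction in form, "the weight will be increased in increments of 1.25–2.5 kg as needed", and the test goes on "until the participant reaches a weight at which they cannot perform all 5 reps of the movement maintaining good form". Then: "Fifty seconds of rest will be provided between attempts". The section gives no starting load, no rule for choosing a step within the range and no maximum number of attempts. It also does not say whether the failing load or the last completed load is recorded.

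The same section treats the other two strength tests differently. For leg dynamometry: "Participants will be instructed to perform this test three times, with a rest of 50 s after each attempt". Each pull lasts 3 s and the best of three is kept. Grip strength follows the same pattern.

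At 12 weeks participants attend "to have their follow-up assessment following the procedures detailed above" (Follow-up assessment). The Blinding section says that assessors cannot be blinded once the intervention has started. The secondary objectives include the between-group difference in "strength (five repetition maximum [5RM] bench press, leg dynamometry, grip strength" (Aims and objectives). Table 4 and its footnote make the bench press a trained exercise in the resistance and combined programmes.

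**The concern.** A rest of 50 s is easier to defend between three brief single pulls than between sets of up to five repetitions at rising load. The two kinds of test also differ in structure. Where the best of three attempts is kept, a tired last attempt does no harm. In an ascending test the decisive attempt is always the last one, so nothing in the scoring removes fatigue from the earlier sets.

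The amount of prior work is not controlled either. A two-fold range of step sizes with no rule means that two assessors, or one assessor at two visits, can take the same woman to the same load after quite different numbers of sets. At follow-up that choice is made by someone who knows her arm.

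At stake is one secondary comparison. If the prior work differs between visits or arms, the 5RM difference mixes strength with tolerance of repeated sets. The pilot is meant to try out procedures for a definitive trial, so a weak test procedure could be carried forward.

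**Working it through.** The protocol gives no figure for the 5RM (no expected gain, variance or power), so there is nothing to reproduce. What can be checked is how the stated rule behaves.

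**Inputs from the protocol article:** step 1.25–2.5 kg; rest 50 s; stop when five good-form repetitions fail; same procedure at follow-up.

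**Assumptions (not in the protocol):** starting load 20 kg; true baseline 5RM spread evenly over 24–36 kg; true gain 7.5 kg; loss of available strength per prior set f = 0 to 2%; one constant step size within a test; last completed load recorded.

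**Step 1: number of sets.** Sets up to and including the 5RM = (5RM − start)/step + 1.

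- 5RM of 25 kg: (25 − 20)/2.5 + 1 = 3 sets, or (25 − 20)/1.25 + 1 = 5 sets.
- 5RM of 35 kg: (35 − 20)/2.5 + 1 = 7 sets, or (35 − 20)/1.25 + 1 = 13 sets.

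So step choice alone moves the set count from 3 to 5, or from 7 to 13, for the same woman at the same visit. With the start held at 20 kg, a 7.5 kg gain adds 7.5/2.5 = 3 sets or 7.5/1.25 = 6 sets.

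**Step 2: effect on the measured gain.** Available 5RM after k prior sets = true 5RM × (1 − f)^k. The load rises one step at a time until it exceeds the available 5RM. The table gives the mean measured gain for a true gain of 7.5 kg; understatement = (7.5 − measured)/7.5.

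| f per prior set | Step (kg) | Start 20 kg at both visits | Start raised by the gain |
|---|---|---|---|
| 0 | either | 7.50 (0%) | 7.50 (0%) |
| 0.5% | 2.5 | 6.93 (8%) | 7.39 (1%) |
| 0.5% | 1.25 | 6.32 (16%) | 7.26 (3%) |
| 1% | 2.5 | 6.32 (16%) | 7.28 (3%) |
| 1% | 1.25 | 5.52 (26%) | 7.15 (5%) |
| 2% | 2.5 | 5.53 (26%) | 7.19 (4%) |
| 2% | 1.25 | 4.43 (41%) | 7.00 (7%) |

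**Step 3: why the starting load decides the size.** At f = 1%, mean attempts (including the failed one) rise from 5.1 to 7.6 with 2.5 kg steps and a fixed start, and from 7.9 to 12.3 with 1.25 kg steps. If the start rises with the gain, they stay level: 5.1 and 5.0, or 7.9 and 7.7.

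**Step 4: which arms.** Fatigue that is equal in all arms largely cancels in a between-arm difference. Only unequal prior work biases it. Extra sets would fall mainly on women who gain bench press strength, whom one would expect chiefly in the resistance and combined arms. Taken alone, this pulls the contrast with control and aerobic exercise towards no difference.

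**The case against.** The strongest reply is that much of the mechanism has to be assumed, and that an article condensing a fuller test procedure may leave out starting load, warm-up and maximum attempts. That largely stands, and it rules out several stronger readings that a reader might infer.

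- **That attempts are unlimited.** The article states no limit; it does not say that there is none.
- **That stronger women necessarily do more sets.** This needs a similar starting load at both visits. The Follow-up assessment section repeats the procedures, not the load.
- **That a given number of kilograms is hidden.** Every value behind such a figure is assumed. At zero fatigue there is no distortion, and the calculation charges light and near-limit sets alike. The step wording could also mean smaller steps only near the limit, which would reduce the set count.
- **That both arms doing resistance work rehearse short rests.** The statement "Each set of exercises will be followed by a 45-s rest" is in the Resistance section; the Combined section gives no rest interval. Any benefit from that practice would act against the understatement, and nothing in the document allows the two to be weighed.
- **That the strength results as a whole, or the trial, are compromised.** The other two strength tests have fixed attempts. The main outcome is feasibility and acceptability, and the Sample size section names cardiorespiratory fitness as the primary outcome of a future trial.

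What the reply does not remove is what the article does state: multi-repetition sets, 50 s of rest, and a two-fold step range, in a test where the limiting load comes last.

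**Conclusion.** The concern holds in limited form. The stated combination of short rest, free step size and no stated limit on attempts lets the recorded 5RM reflect fatigue as well as strength, with an amount of prior work that varies by step choice under an assessor who is unblinded at follow-up. The step-choice part needs no assumption about the follow-up starting load.

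Understated gains in the arms that train the bench press are conditional on a similar start at both visits. A between-arm bias of known size or certain net direction is not established. The 8–41% and 1–7% ranges illustrate how far the answer depends on the unstated starting load and the unknown fatigue rate; they are not estimates for this trial.

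The change is worth making because it is cheap and the pilot exists to test procedures. It is not a threat to the primary aim.

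**What to change.** In the Muscular strength section:

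1. Lengthen the rest between multi-repetition attempts, for example to 2–3 min. The interval is a proposal, and the sponsor should justify the one it adopts.
2. Set one step rule: larger early steps and one fixed final increment. The final increment is a trade-off. A 2.5 kg step is 10% of a 25 kg 5RM (2.5/25); a 1.25 kg step is finer but can add sets.
3. Set the first load by a rule that ignores arm, such as the response to a standard warm-up set. Setting the follow-up start from expected strength would give an unblinded assessor an arm-dependent expectation to act on.
4. Aim for a similar small number of attempts, for example about five, and apply the whole procedure identically at both visits.
5. Record the last load completed for five good-form repetitions, and the number of attempts, so that differences in prior work can be seen.

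Cost: with five attempts there are four rests. The extra time is 4 × (120 − 50) = 280 s to 4 × (180 − 50) = 520 s, or roughly 5–9 min per assessment, partly offset where fewer attempts are needed. No extra staff or equipment is required.
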